#### Secondary analyses: Predictors of Response to Treatment

As stated previously, long-term low back pain affects 10% of Australians ranging across a heterogeneous group. It is worthwhile to determine predictive factors of patients in order to determine if tai chi would be a beneficial treatment for that individual.

First, we will assess whether any single baseline predictor can identify patients who respond best to Tai Chi. To limit the chance of Type 1 error a limited list of potential predictors has been determined a-priori on the basis of biological rationale, they are: (bothersomeness of back symptoms score measured with the bothersomeness scale, physical function measured with the *patient specific functional scale*, stress level measured with the DASS-21, anxiety level measured with the DASS-21, and the patients self-reported expectation of treatment. A model will be created for the primary outcome measure, bothersomeness of back symptoms and will include the interaction term between treatment allocation (Tai Chi or control) and baseline predictor, as well as, treatment allocation and baseline predictor as terms on their own. The statistical significance and size of the interaction coefficient will be assessed to determine whether the baseline characteristic is able to identify patients who respond best to the treatment.

Second, we will assess if a combination of baseline characteristics is more effective than any single characteristic at identifying patients who respond best to Tai Chi. A multivariate backwards stepwise linear regression model will be used to assess this question. To be considered as a candidate variable for the multivariate analysis the interaction term in the first model (primary analysis) will be required to be associated with outcome (p < 0.25). We will inspect the correlations between the candidate variables and where any correlation is greater than 0.4 we will select one of the variables based on ease of assessment and psychometric properties. Significant variables will be entered into the multivariate model. A p-value for interaction terms > 0.05 will be used to remove both the predictor and its interaction from the model. We will assess whether the final model can be simplified to create a rule which is appropriate for use in a clinical setting.

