### Sample Size

We have designed the study to detect a clinically important difference of 1.5 units on the 0–10 bothersomeness scale (estimate for SD = 2.35), 1 unit on the 0–10 pain numerical rating scale (estimate for SD = 2), 1 unit on the 0–10 patient specific functional scale (estimate for SD = 1.8); 1 unit on the 0–10 Global Perceived Effect Scale (estimate for SD = 1.65), 4 units on the 24 item Roland Morris Disability Questionnaire (estimate for SD = 4.9). We have taken the SD estimates from trials that recruited a similar patient cohort [3,29,40]. Given these considerations we have chosen to design the study to detect an effect size of 0.5 SD. Based upon the results of a similar trial by our group [3] we have allowed for 15% non-compliance with treatment, 15% loss to follow-up, and assumed a correlation between baseline and change scores of outcomes of 0.5. Taking these factors into account with specifications of alpha = 0.05, power = 0.80 a sample size of 77 participants per group is required to detect an effect size of 0.50 SD [41]. Accordingly we will recruit 80 participants per group or 160 participants in total to allow for treatment in blocks of 8. Blocks of 8 allow us to randomize 4 subjects at the one time to the Tai Chi group and so have a sufficiently large class.

As a secondary analysis we will evaluate predictors of response to treatment. We estimate that it would require ~640 subjects to detect an interaction effect of the same magnitude as the main effect. We do not have the resources for such a study. Accordingly we acknowledge that we may miss an interaction effect in our analyses. Brookes and colleague's simulations demonstrate that when testing for effect modification, trials have the same power to detect an interaction effect that is twice the size of the main effect [42].

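### The predictor analysis drops baseline bothersomeness as a covariate unless it modifies the treatment effect, and five unadjusted interaction tests carry about a one-in-five chance of a false modifier

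*Protocol article*

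**What the plan says.** Protocol article, Secondary analyses: Predictors of Response to Treatment. Five baseline candidates are named: bothersomeness, patient-specific function, stress, anxiety and treatment expectation. The reason given for the short list is: "To limit the chance of Type 1 error a limited list of potential predictors has been determined a-priori".

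Step one fits a model for bothersomeness for each candidate, with treatment, the candidate and their interaction. To go forward, "the interaction term in the first model (primary analysis) will be required to be associated with outcome (p < 0.25"). Where two candidates correlate above 0.4, one is kept.

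Step two is backward elimination in a multivariable linear model, under this rule: "A p-value for interaction terms > 0.05 will be used to remove both the predictor and its interaction from the model". The section closes: "We will assess whether the final model can be simplified to create a rule which is appropriate for use in a clinical setting". It states no multiplicity adjustment and no validation step.

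The Sample Size section calls this a secondary analysis and says: "We estimate that it would require ~640 subjects to detect an interaction effect of the same magnitude as the main effect". It accepts that an interaction may be missed, and adds that power is kept for an interaction twice the size of the main effect.

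**The concern.** The removal rule treats a predictor's interaction and its main effect as one unit, but they answer different questions. A non-significant interaction says that the predictor does not visibly change the treatment effect. It says nothing about whether the predictor explains variation in the outcome. The baseline value of the outcome commonly explains much of that variation, and the Sample Size section relies on such a correlation. The predictor analysis then discards it in the setting where power is shortest.

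The second issue is error control. A list of five limits the number of tests, but each is still judged at 0.05. The article discusses the risk of missing a modifier. Apart from the short list, it does not address the risk of reporting a false one, although the end product may be a rule for choosing who is offered tai chi.

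**Working it through.** **Inputs.** From Sample Size: "we have chosen to design the study to detect an effect size of 0.5 SD"; "allowed for 15% non-compliance with treatment, 15% loss to follow-up, and assumed a correlation between baseline and change scores of outcomes of 0.5"; "specifications of alpha = 0.05, power = 0.80 a sample size of 77 participants per group is required"; 160 recruited. Two-sided testing is assumed. After 15% loss, 160 × 0.85 = 136 are analysed.

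**The plan's own figures.**
- Per group before adjustments: 2 × (1.960 + 0.842)² / 0.5² = 62.8.
- Times 1 − 0.5² for the correlation: 47.1.
- Divided by 0.85 for loss: 55.4.
- Divided by 0.85² for dilution through non-compliance: 76.7, so 77. This matches. Of the variants tried, none without the correlation factor gives 77 (they give 63, 74, 87 or 103).
- 4 × 160 = 640 matches the figure for the interaction. At a quarter of the required size, power is Φ(2.802/2 − 1.960) = Φ(−0.559) = 29%.

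**How often baseline bothersomeness is lost.** If it does not modify the effect, its interaction p-value is uniform. It fails the screen with probability 0.75, and a further 20 or so percentage points go at elimination, leaving about 5%. Simulations of the stated procedure (136 or 160 analysed; predictors uncorrelated, correlated 0.3, or correlated 0.2 with stress and anxiety at 0.6) give 94-95%. With a true baseline interaction of 0.25 SD per SD the loss falls to about 63%, and with 0.5 to about 10-11%.

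**What the loss costs.** Residual variance rises by the factor 1/(1 − r²), and standard errors by its square root. The r here is an assumption. The article gives 0.5 for baseline with change scores and no figure for baseline with follow-up.

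| r | Variance | SE |
|---|---|---|
| 0.3 | +10% | +5% |
| 0.5 | +33% | +15% |
| 0.7 | +96% | +40% |

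In simulation at r = 0.5 with 136 analysed, keeping baseline bothersomeness in both steps raises power for a true interaction with another predictor. The gain is from 39% to 48% at 0.3 SD per SD, and from 80% to 89% at 0.5. The false-modifier rate is essentially unchanged.

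**False modifiers when none exists.**
- Five independent tests: 1 − 0.95⁵ = 22.6%.
- Simulating the stated procedure: mostly 20-23%, with 18% in the lowest scenario (160 analysed, stress and anxiety correlated 0.6, so the 0.4 rule drops one of them).
- Effect of the screen (136 analysed, same correlations): 21% with a 0.05 screen, 20% with 0.25 and 17% with none.
- A Bonferroni threshold of 0.05/5 = 0.01: 1 − 0.99⁵ = 4.9% by formula, 4.3-5.0% in simulation with all main effects kept.

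**What the lower threshold costs.** For a true baseline interaction of 0.5 SD per SD with 136 analysed, power is 67% at 0.01 in the joint model, against 89% under the plan's procedure.

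**The case against.** This is a labelled secondary analysis with a short pre-specified list, and the article is candid about low power. Removing a predictor together with its interaction keeps the model hierarchical and, under randomisation, does not bias the treatment effect. The primary mixed model is untouched. The 95% figure holds only when baseline bothersomeness is not a modifier, and most of it comes from the screen. With independent tests, another interaction survives in the final model while baseline is absent in only 0.95 × (1 − 0.95⁴) = 18% of trials with no true interaction, so the 95% and the 15% wider standard errors often do not coincide there. Multiplicity handling may also sit in an analysis plan that is not shown.

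All of that stands, and it limits the point. It does not remove it. Hierarchy requires the main effect while the interaction is in the model; it does not require deleting the main effect when the interaction goes. The precision loss also acts at step one, where the other four candidates are screened without the baseline outcome. The article itself fixes the removal rule, the 0.05 threshold and the possible clinical rule.

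Four stronger readings are not supported:
- A reader might infer that a false modifier is likely. At about one in five, most null trials produce none. Nor can it be said that any predictor found is probably a chance finding; that depends on how many true interactions exist.
- The lenient screen might be blamed. It is not the cause, because survival still requires p ≤ 0.05.
- A reader might conclude that the plan calls its own sample four-fold too small. The figure of about 640 applies only to an interaction as large as the main effect, the limitation is acknowledged, and low power does not raise the false-positive rate.
- The article might be read as claiming control of type I error. It claims only to limit it, which a short list does.

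**Conclusion.** The point holds in a limited form. Followed as written, the predictor analysis leaves baseline bothersomeness out of its final model in about 95% of trials when that variable is not a modifier, and out of the single-predictor models for the other four candidates. At an assumed correlation of 0.5 this costs about 15% in standard error (5% to 40% over r = 0.3 to 0.7), or roughly 9 percentage points of power in the two cases simulated. It causes no bias and does not reach the primary analysis.

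Separately, the chance of at least one false modifier when none exists is about 20-23%, roughly four times 5%. The cause is five unadjusted tests, and the acknowledgement in the Sample Size section covers only missed interactions. A model with that risk should not be presented as a clinical rule without validation. The simulated figures rest on the assumed predictor correlations and on 136 or 160 analysed participants.

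**What to change.** In Secondary analyses: Predictors of Response to Treatment:

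1. Keep baseline bothersomeness as a main effect in every single-predictor and multivariable predictor model, whatever its interaction p-value. This must override the p < 0.25 screen as well as the elimination rule, since most of the loss happens at the screen.
2. Let a non-significant interaction remove only the interaction term.
3. Report all five interaction estimates with 95% confidence intervals, and state the roughly one-in-five chance of at least one spurious modifier.
4. Replace the clinical-rule sentence with a statement that any model is hypothesis-generating and needs validation in another trial before clinical use.

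A Holm or Bonferroni threshold is optional. Bonferroni brings the false-modifier risk to about 5%, but at a notable price in power (67% against 89% in the case above), so it is a trade-off to decide and state.

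The cost is revised wording, slightly different code and no ready-to-use clinical rule from this trial. No new data are needed.

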## Discussion

This study will evaluate the effects of a 10-week tai chi exercise program on people with long-term low back pain. The study is adequately powered to detect change in the primary and secondary outcomes that include bothersomeness of back symptoms, self-reported disability and physical function and global perceived effect of treatment. The focus of this study is to determine the efficacy of tai chi as an intervention for long-term low back pain; it aims to provide both health care providers and patients with evidence-based advice for treatment planning. To our knowledge this is the largest study specifically designed to examine the effect of tai chi on low back symptoms in people with long-term low back pain.
